### Goals of This Study

This research project has 2 general objectives and 6 specific aims.

First, we seek to understand the meaning and implications of living with CP for women experiencing IPV compared to those with CP alone. From this point forward, the term “women with CP alone” will refer to women who have never experienced any form of psychological, physical, or sexual violence at any stage of their lives, whether perpetrated by an intimate partner or another known or unknown individual. We include other forms of violence beyond IPV against women because they may also influence CP management and health outcomes [31].

More specifically, by comparing women with CP and exposure to IPV to women with CP alone, we aim to (1) examine how CP affects their daily lives, (2) identify the impact that CP may have on their intimate relationship and vice versa, (3) understand how they self-manage CP, and (4) describe their experiences with health systems.

Second, we aim to determine whether women with CP alone, women with CP who are currently experiencing IPV, and women with CP who have a past history of IPV present distinct profiles based on risk and protective factors for disabling CP and health outcomes. If differences exist, we will also (5) identify the factors that best explain these profiles and (6) detect more specific subprofiles within each group.

Ultimately, the findings will be used to develop assessment and intervention guidelines for health and social service professionals.

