#### Data Analysis

Inferential statistics help researchers draw conclusions about populations based on sample data, providing insights into social phenomena [153]. Machine learning, as a subset of artificial intelligence (AI) techniques, analyzes large datasets to identify patterns and make predictions [154]. These methods are transformative in gender studies, uncovering patterns in gender-related data and deepening the understanding of social inequalities and biases [155]. These methods have been successfully applied to areas such as forecasting gender-based violence, further demonstrating their relevance in social sciences [156].

Exploratory data analysis (EDA) will be crucial in examining CP and its connection to past or current IPV against women. EDA uses techniques such as scatterplots, clustering algorithms, and principal component analysis to investigate multidimensional datasets [157]. Scatterplots help identify correlations between sociodemographic variables, clustering algorithms reveal subgroups within the population, and principal component analysis reduces dimensionality to uncover latent factors such as the relationship between gender identity and social support [158]. The use of EDA will allow us to detect groups and subgroups at a glance by creating subclusters, that is, more specific profiles in each of the groups.

Inferential statistical methods will be applied to differentiate between women with CP alone and those with CP who have experienced IPV in the past or are currently experiencing IPV. Hypothesis testing, estimation, and prediction techniques will be used to make comparisons, with visual tools such as boxplots for examining variable distributions across groups. We will use 2-tailed *t* tests and ANOVA to compare means across groups [159].

Feature ranking techniques will help identify the most relevant variables for accurate classification. Methods such as information gain, gain ratio, Gini index, and relief will determine the importance of features such as education, socioeconomic status, pain level, and social support [160]. This feature ranking will help prioritize the most influential factors affecting each group, including those based on country distribution.

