Machine learning classifiers, including random forest, decision trees, adaptive boosting, gradient boosting, and support vector machines, will be applied to classify data. The process will involve training, validation, and testing phases, with hyperparameter tuning during validation. K-fold cross-validation will be used to evaluate the model’s performance, using training, validation, and testing phases across different folds [161]. The model’s performance will be assessed using metrics such as precision, recall, *F*_1_-score, and receiver operating characteristic curves [162].

Feature importance evaluation will identify which variables most significantly influence the model’s predictions. This analysis, combined with explanatory models such as Shapley additive explanations, will provide further insights into how features impact classification outcomes [163]. These methods are widely used in gender studies to uncover social patterns and inequalities. By combining Shapley additive explanations values with EDA, we aim to pinpoint the most significant factors that explain different profiles in the data [164].

Data analysis will be conducted using Python (Python Software Foundation), with libraries such as *pandas* (for data manipulation), *NumPy* (for numerical operations), *scikit-learn* (for machine learning), and the combination of *matplotlib* and *seaborn* (for visualization). This suite of tools provides an efficient framework for inferential statistical analysis and exploratory data. Comparable analysis could also be performed using R (R Foundation for Statistical Computing), which presents similar usability for data study. R comes with *tidyverse*—a package that merges *dplyr* and *ggplot2* for visualizing data—and *caret* for building predictive models. Similar software such as MATLAB (The MathWorks, Inc) also allows for wider functionality for statistical computing and algorithm development.

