Second, we aim to identify whether women with CP alone, those with CP and currently experiencing IPV, and those with CP and a past history of IPV present different profiles based on risk and protective factors for (disabling) CP and health outcomes. We hypothesize that women with CP and current or past experiences of IPV will show higher levels of disabling pain, more excessive persistence or avoidance activity patterns, lower levels of exercise, worse pain-related self-efficacy, greater pain worrying, informal social support that fosters dependence, lower levels of physical functioning, greater anxiety and depression, poorer medication management, increased illegal drug use, more suicidal thoughts and attempts, and a higher frequency of health system use. This hypothesis is based on previous findings indicating higher levels of disabling pain in women experiencing IPV compared to those with CP alone, as well as higher levels of suicidal thoughts, addiction issues, and greater use of health services compared to the general female population [23,165]. These characteristics will likely worsen in the presence of PTSD [82]. In addition, because pain-related self-efficacy and pain worrying have been linked to CP [65-69,78], we expect these factors to most effectively account for the profiles of women with a current or past history of IPV, along with informal social support, for the aforementioned reasons.

Moreover, because AI techniques go beyond traditional inferential statistics, it can identify patterns and relationships between variables that might remain undetected by the human eye. AI may uncover specific profiles within different groups of women, revealing how factors such as educational background, traditional feminine roles, ethnicity, and the duration of violence intersect with CP-related variables; for example, it could be that the pattern of excessive persistence is more common in women who are in the initial stages of the relationship and that they may seek to conform to traditional gender roles in an effort to meet their aggressors’ expectations. AI’s ability to process large datasets could lead to new insights and advances in understanding pain, its management, and its relationship with other concurrent psychosocial factors.

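### No conventional multivariable model is named beside the five machine-learning classifiers, so the article offers no like-for-like reference for aim 5 or for what machine learning adds

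*Protocol article*

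**What the plan says.** All references are to the protocol article.

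- **Goals of This Study.** If the three groups differ, aim 5 is to "identify the factors that best explain these profiles".
- **Data Analysis (phase 2), conventional side.** In general terms, "Hypothesis testing, estimation, and prediction techniques will be used to make comparisons". The specific procedures named are 2-tailed t "tests and ANOVA to compare means across groups".
- **Data Analysis, exploratory side.** "EDA uses techniques such as scatterplots, clustering algorithms, and principal component analysis to investigate multidimensional datasets". Feature ranking by information gain, gain ratio, Gini index and relief is also planned.
- **Data Analysis, supervised models.** "Machine learning classifiers, including random forest, decision trees, adaptive boosting, gradient boosting, and support vector machines, will be applied to classify data". On validation, "K-fold cross-validation will be used to evaluate the model’s performance", with tuning during validation. On reporting, "The model’s performance will be assessed using metrics such as precision, recall", the F1-score and ROC curves. Feature importance and Shapley values are then to show which variables drive the classification.
- **Discussion, Summary.** Pain-related self-efficacy, pain worrying and informal support are expected to account best for the profiles of the IPV groups. The section adds that "because AI techniques go beyond traditional inferential statistics, it can identify patterns and relationships between variables that might remain undetected by the human eye".

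**The concern.** Aim 5 and the hypothesis that goes with it are joint questions: among scales that are likely to be correlated with one another, which carry the separation between groups? A t test or ANOVA on each scale cannot answer that. Under the methods named, the answer has to come from importance measures and Shapley values computed on flexible classifiers. No adjusted association from a conventional model stands beside them.

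The same gap affects how machine learning is credited. The named conventional tests look at one variable at a time; the named classifiers use all variables together. If a factor shows up in the second set and not in the first, two explanations are mixed: the analysis was multivariable, or it was machine learning. Only a conventional multivariable model on the same predictors separates the two. Without it, a report could present as an AI insight something that ordinary regression would also have shown.

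**Working it through.** **1. Count of named methods in the phase 2 Data Analysis section**

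| Type | Named | Number |
|---|---|---|
| Conventional inferential tests, one variable at a time | t tests, ANOVA | 2 |
| Unsupervised multivariate methods | clustering, principal component analysis | 2 |
| Supervised multivariable classifiers | random forest, decision trees, adaptive boosting, gradient boosting, support vector machines | 5 |
| Conventional multivariable models | none | 0 |

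Clustering and principal components describe structure but give no adjusted comparison between groups. Of the feature rankings, information gain, gain ratio and Gini index also score variables singly.

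**2. Inputs for the illustration**

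- From Sample Size Calculation: 193 women with CP alone, 83 with current and 83 with past IPV. Any IPV = 83 + 83 = 166; total = 193 + 166 = 359.
- The 83 and 193 are close to reproducible: 40% against 20%, two-sided 5%, 90% power, ratio 7:3, with continuity correction, gives 83 and 193.7. The point does not depend on this.
- Assumed, since the article gives no such values: two normal factors with within-group correlation r; groups differ by d SD on the first factor and not at all on the second.

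**3. One-variable analysis.** The second factor has no marginal difference, so the t test rejects at about its nominal 5%. In 1,500 simulated studies it did so in about 4%.

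**4. Joint analysis by ordinary regression.** Given the first factor, the second differs between groups by r·d/√(1 − r²) residual SD. With r = 0.5 and d = 0.5:

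- adjusted difference = 0.25/√0.75 = 0.289
- 193 × 166/359 = 89.24
- share of group membership explained by the first factor: d²pq/(1 + d²pq), with pq = (193/359)(166/359) = 0.2486, so 0.0621/1.0621 = 0.0585
- expected z = 0.289 × √(89.24 × 0.9415) = 2.65
- approximate power = Φ(2.65 − 1.96) ≈ 0.75

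Simulation with ordinary logistic regression gave about 76%, in agreement.

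**5. Range.** Over r = 0.3–0.6 and d = 0.4–0.5, logistic regression detects the second factor in about 22% to 92% of simulated studies. The formula gives 21% at r = 0.3, d = 0.4 (z = 1.17) and 93% at r = 0.6, d = 0.5 (z = 3.44).

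**6. The same point for discrimination.** With K factors, each differing by d and equally correlated r, a single factor has AUC Φ(d/√2), and an additive linear model has Φ(√(Kd²/[2(1 + (K − 1)r)])). For d = 0.3, K = 10, r = 0.3 these are Φ(0.212) = 0.584 and Φ(√(0.9/7.4)) = Φ(0.349) = 0.636. The joint model gains with no interaction or non-linearity in the data, so a gain over single variables is not in itself evidence of anything specific to machine learning.

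**The case against.** The strongest reply has four parts.

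- **The lists are open.** The classifier list begins with the word including, and estimation and prediction techniques are left general. This is also a condensed article, and a full analysis plan may name a regression. That stands: the point is what the article names, not proof that no regression will be fitted.
- **The AI statement is a rationale.** A reader might infer that the study sets out to show AI superior and that this will look true by default. The documents do not support that. The sentence is in the Discussion, no aim or hypothesis pits AI against conventional statistics, and no head-to-head comparison is planned. Nor is the claim uncheckable: cross-validated metrics could show poor classification, and a regression could be run later on the same data. What those metrics cannot show is whether a simpler model does as well, and a reference chosen after the results are known carries less weight.
- **The classifiers need not be worse.** A reader might infer that they would separate the groups less well than plain regression. That holds only under assumptions such as purely additive effects and untuned models, whereas the plan tunes. In one additive simulation (40 factors correlated 0.3, 12 of them shifted in the same direction by 0.40 SD for current and 0.25 SD for past IPV), ridge logistic regression had AUC 0.735 and a tuned support vector machine 0.730. With real interactions, which the Discussion has in mind, a classifier could do better. No ranking is claimed here.
- **The illustration is a chosen case.** The second factor has exactly zero marginal difference. True; it shows that the confusion can arise, not how often it will.

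**Conclusion.** The concern holds in limited form. The article names one-variable tests and five classifiers, and no conventional multivariable model, although aim 5 and its hypothesis are about the joint contribution of factors and the Discussion asserts that AI adds to traditional inference. A factor found by a classifier but missed by a t test therefore cannot, on the methods named, be attributed to machine learning rather than to joint analysis. In the illustrated case the gap between the t test and ordinary regression is about 4% against 76% (22% to 92% for regression over the assumed range). These sizes rest on assumed correlations and effects, on normal factors, and on pooling the two IPV groups. This is a cheap improvement to the stated analysis, not a flaw that invalidates the study.

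**What to change.** In the phase 2 Data Analysis section, alongside the classifiers:

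1. Prespecify a penalised (for example ridge) main-effects multinomial logistic regression for the three groups, on the same predictors, tuned and evaluated in the same folds as the classifiers. Penalisation is advisable because the smallest groups have 83 women; with, say, 40 predictors (an assumption) that is 83/40 ≈ 2.1 women per coefficient in each logit.
2. Report its cross-validated performance and each classifier's difference from it.
3. For aim 5, report its coefficients on standardised predictors beside the Shapley values.
4. State that if no classifier clearly improves on it, the factors separating the groups will not be described as findings that conventional statistics would miss.

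Item 4 concerns the factors that separate the groups; it does not decide whether a subprofile under aim 6 is real.

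Cost: one more model, available in scikit-learn, which the article already names. The timeline puts analysis in year 3, after the questionnaires, so the reference can be fixed before results are seen. The downside is that the apparent advantage of AI may be smaller or absent.

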## Results

As of May 2025, we had contacted relevant associations to present the project and begin recruiting voluntary participants. We have conducted the pilot study to assure the adequacy of the questionnaire and usability or technical functionality of the web-based platform. The results are expected to be published starting in January 2026. The study timeline is presented in Table 3.

**Table 3 table3:** Study timeline.

Year, study phases, and tasks				Months																						
				1		2		3		4		5		6		7		8		9		10		11		12
**Year 1**																										
	**Phase 1**																									
		Identification of and contact with associations and support centers for IPV^a^ against women, CP^b^ associations, CP units, and primary health care centers to present the projects and request their collaboration for phase 1 and phase 2	✓		✓																					
		Development of semistructured interview guide					✓																			
		Conducting interviews							✓		✓															
		Transferring data											✓													
		Data analysis													✓				✓							
		Writing articles and communications																	✓		✓		✓		✓	
**Year 2**																										
	**Phase 2**																									
		Contact with associations and support centers for IPV against women, CP associations, CP units, and primary health care centers to initiate participation in phase 2	✓		✓																					
		Design of web-based questionnaire	✓		✓																					
		Questionnaire piloting and inclusion of changes					✓																			
		Supervision of questionnaire completion							✓		✓		✓		✓				✓		✓		✓		✓	
**Year 3**																										
	Data analysis			✓		✓		✓																		
	Writing articles and communications									✓		✓		✓		✓				✓		✓		✓		✓
	Develop assessment and intervention guidelines																			✓		✓		✓		

^a^IPV: intimate partner violence.

^b^CP: chronic pain.

## Discussion

### Summary

This project has 2 main aims. The first is to acquire knowledge on the meaning and implications of living with CP for women experiencing IPV compared to those with CP alone. In this regard, we hypothesize that (1) women who experience any form of IPV (psychological, physical, or sexual) will report a greater daily impact of CP on their functionality than those with CP alone; (2) compared to the latter, the former will report a stronger bidirectional relationship between CP and intimate relationship dynamics as well as worse health outcomes (ie, episodes of violence will increase CP symptomatology and vice versa), with such a negative cycle being more prevalent; and (3) CP management and experiences with the health system will be better among women with CP alone. Hypotheses 1 and 3 are based on the fact that some authors have highlighted that the impact of IPV against women on the health of those affected adds to CP [31]. This could impair their ability to self-manage CP, leading to increased medication use and more frequent visits to health centers [165]. We believe that this result will be independent of the type of violence experienced because studies have shown that psychological violence alone can negatively impact CP severity and disability [166,167].

Regarding our second hypothesis, we expect that aggressors will present more hostility and criticism toward their partners’ health conditions as a way to undermine them, increase dependence, and control them, considering violence as an instrumental component [165]. We also expect that periods of violence will be linked to an increase in CP symptomatology. However, in women with CP alone, their partners will likely promote autonomy by encouraging and reinforcing healthy behaviors or promote dependence by maintaining disabling pain behaviors through solicitousness. In this group of women, even if hostile responses can also be present sometimes, their impact on CP will be less significant because they need to take place in a context of low marital satisfaction [95,96], and we assume that levels of marital satisfaction will be higher among women with CP alone. In addition, we expect that periods with an increase in CP symptomology will be more related to external stressors than to the relationship itself.

Second, we aim to identify whether women with CP alone, those with CP and currently experiencing IPV, and those with CP and a past history of IPV present different profiles based on risk and protective factors for (disabling) CP and health outcomes. We hypothesize that women with CP and current or past experiences of IPV will show higher levels of disabling pain, more excessive persistence or avoidance activity patterns, lower levels of exercise, worse pain-related self-efficacy, greater pain worrying, informal social support that fosters dependence, lower levels of physical functioning, greater anxiety and depression, poorer medication management, increased illegal drug use, more suicidal thoughts and attempts, and a higher frequency of health system use. This hypothesis is based on previous findings indicating higher levels of disabling pain in women experiencing IPV compared to those with CP alone, as well as higher levels of suicidal thoughts, addiction issues, and greater use of health services compared to the general female population [23,165]. These characteristics will likely worsen in the presence of PTSD [82]. In addition, because pain-related self-efficacy and pain worrying have been linked to CP [65-69,78], we expect these factors to most effectively account for the profiles of women with a current or past history of IPV, along with informal social support, for the aforementioned reasons.

Moreover, because AI techniques go beyond traditional inferential statistics, it can identify patterns and relationships between variables that might remain undetected by the human eye. AI may uncover specific profiles within different groups of women, revealing how factors such as educational background, traditional feminine roles, ethnicity, and the duration of violence intersect with CP-related variables; for example, it could be that the pattern of excessive persistence is more common in women who are in the initial stages of the relationship and that they may seek to conform to traditional gender roles in an effort to meet their aggressors’ expectations. AI’s ability to process large datasets could lead to new insights and advances in understanding pain, its management, and its relationship with other concurrent psychosocial factors.

### Limitations

This study is not without limitations. One of the main challenges is the high number of participants required for the quantitative study. To mitigate this issue, we will contact primary health care centers, associations and support centers for IPV against women, CP associations, and CP units across the province of Alicante. A second limitation is the use of nonprobability sampling, which may introduce bias. However, this research aims to provide a preliminary understanding of the co-occurrence of these 2 significant health issues; to the best of our knowledge, it will be the first to do so with a large sample using AI. A third limitation concerns the number of questionnaires that need to be completed in the second study. To address this, participants’ responses will be saved, and they will be given ample time to complete all questionnaires. In addition, the order of presentation will be randomized to reduce the likelihood that the same questionnaires are consistently left unanswered. We hope this will result in a similar number of responses across all questionnaires. To further encourage questionnaire completion, we will ask the center directors and professionals to remind participants about the importance of answering all questions.

A fourth limitation is the focus on only individual and relational factors. While community and societal factors also influence CP and its disabling effects [168], the primary aim of this study is to enhance the detection and treatment of CP in health care settings by personalizing care. Therefore, the focus is placed on individual and relational factors. Finally, not all scales have been validated with Spanish samples. Validating several scales has high costs and is time consuming, but we will conduct translation and back-translation procedures and test the instruments directly with the population. Moreover, the study will only be conducted in the province of Alicante. However, if profiles are identified, we plan to extend the second study to other Spanish regions as well as other countries while controlling for other macrovariables (eg, free access to the health system) to analyze the commonalities and differences in the profiles. If minimal or no differences are found, the profiles could be largely explained by the experience of IPV against women, and recommendations could be generalized to similar countries.

